## 2. Methods and analysis

### 2.1. Study design

This is a cluster-randomized, two-arm parallel, multicenter, open-label, controlled clinical trial that will be conducted in PC centers of the Andalusian Health Service located in the province of Córdoba (Spain). PC professionals will be randomized to one of two study groups (Figure 1): (1) Experimental Group (EG): Professionals will implement an approach based on brief motivational intervention (18) applied on patients with risky alcohol use, receiving previously a specific training program in this field; (2) Control Group (CG): Professionals will also receive prior training on the management of the patient with risky alcohol consumption and will implement the usual clinical care (health advice) in recruited patients. Participants in both groups will attend a workshop focused on the identification and management of patients with risky alcohol consumption.

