#### 2.1.1. Eligibility criteria

##### 2.1.1.1. Professional selection criteria

Inclusion criteria will be: (1) To be a PC healthcare professional (family physician, nurse or resident internal specialist in Family and Community Medicine or Nursing); (2) To provide informed consent to participate in the clinical trial.

Exclusion criteria will be: Prior MI skills or refusal to participate in the study.

At least 50 healthcare professionals will participate in the controlled clinical trial, each of them will recruit 7–8 patients in PC through opportunistic search.

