#### 2.1.3. Random assignment

The randomization unit will be the healthcare professional, and the intervention unit will be the patient. Professionals will be randomly assigned and equally (1:1) to one of the two study groups (EG or CG), stratifying according to the center and type of professional. Patients will be recruited through consecutive sampling (opportunistic search of subjects who are treated at participating health centers).

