### 2.3. Statistical analysis

An intention-to-treat analysis will be performed to control the effects of losses and dropouts, dragging for analysis the data from the last observation obtained. Survey data will be automatically processed on Google Drive, directly by each of the participating researchers. They will then be exported to an Excel sheet from Google Drive and statistically treated with the SPSS v. 17.0. A descriptive analysis and an initial comparability analysis of the groups will be conducted. Confidence intervals of 95% will be calculated for the major study estimators. A bivariate analysis will be conducted to assess the relationship of the independent variables and the effect of the intervention, for which the Chi-square test will be used, the mean comparison test for independent samples, such as Student *t* test or ANOVA (after verification of normality by using the Kolmogorov-Smirnov test); bilateral comparisons were used, and a value of *p* ≤ 0.05 will be considered. A multivariate analysis will then be performed to determine which sociodemographic, work, and care factors are associated with the intervention developed, controlling the predictors and/or confounders by multiple linear regression and unconditioned binary logistic regression.

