### 2.4. Sample size

Based on a previous study performed by our team members (26), and to find a 20% difference between the percentage of patients in abstinence (partial or total) between EG (37%) and CG (20%), for an alpha error of 5%, and statistical power of 80%, the size would be 220 subjects (110/group). Since it is a cluster randomization system, we will consider the “design effect” and we will assume a loss rate of 5%. Estimates of the intra-cluster correlation coefficient (ICC) in ECC by clusters in PC show that they are generally less than 0.05 (27). This ICC translates, for a cluster size of 15, into a design effect corresponding to a factor of 1.7. Assuming this value, the size would be 394 subjects to recruit (197 in each group).

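### Professionals are randomised, but section 2.3 names only methods for independent observations; applied to the patient outcomes, a nominal 5% test has a true error of about 6% to 9%

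*Protocol article*

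**What the plan says.** - **Design and unit.** Section 2.1: "This is a cluster-randomized, two-arm parallel, multicenter, open-label, controlled clinical trial". Section 2.1.3: "The randomization unit will be the healthcare professional, and the intervention unit will be the patient". Allocation is 1:1, stratified by centre and type of professional.
- **Cluster numbers.** Section 2.1.1.1: "At least 50 healthcare professionals will participate in the controlled clinical trial, each of them will recruit 7–8 patients in PC through opportunistic search".
- **Sample size.** Section 2.4 recognises the correlation ("Since it is a cluster randomization system, we will consider the “design effect"). It takes the ICC to be generally below 0.05 and applies a factor of 1.7, based on 15 patients per cluster, to reach 197 per group.
- **Analysis.** Section 2.3 is one general paragraph. Its bivariate step is one "for which the Chi-square test will be used, the mean comparison test for independent samples", such as Student's t or ANOVA. Its multivariable step uses "multiple linear regression and unconditioned binary logistic regression". Tests are two-sided at 0.05, with 95% intervals.
- **Outcomes.** Section 2.5.1 lists primary outcomes of two kinds. Those in patients are drinks on a typical day, frequency of heavy-drinking days and the AUDIT total. Those in professionals are EVEM, CICAA, and awareness and attitude. Section 2.3 does not say which method serves which kind.

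**The concern.** Patients of one professional share that professional's skill, style and practice population, so their outcomes are correlated. The sample size section accepts this; the analysis section proceeds as if the correlation were zero. A method that counts each patient as an independent unit gives the arm comparison too small a standard error. P-values are then too small and intervals too narrow. The outcomes affected are the patient-level primary ones, on which the claim of effectiveness rests. A result just under 0.05 could owe its significance to the analysis and not to the intervention.

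**Working it through.** **1. The plan's own figure.** With 37% against 20%, two-sided 5%, 80% power and no continuity correction, the mean proportion is 0.285:

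n = [1.96·√(2·0.285·0.715) + 0.8416·√(0.37·0.63 + 0.20·0.80)]² / 0.17² = 109.5, so 110 per group.

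Design effect DE = 1 + (15 − 1)·0.05 = 1.70; 110·1.70 = 187; 187/0.95 = 196.8, so 197 per group and 394 in all. Section 2.4 reproduces exactly. Clustering is therefore accounted for in recruitment, and only there.

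**2. Inputs for the planned trial.** Patients per professional m = 394/50 = 7.88, in line with the 7–8 of section 2.1.1.1. The ICC is at most 0.05 by section 2.4. The article gives no lower value, so 0.01 to 0.05 is my assumed range.

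**3. Formulas.** DE = 1 + (m − 1)·ICC. True two-sided error of a nominal 5% test = 2·[1 − Φ(1.96/√DE)]. Correct interval width divided by unadjusted width = √DE.

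| m | ICC | DE | True error | Correct / unadjusted width |
|---|---|---|---|---|
| 7.88 | 0.01 | 1.069 | 5.8% | 1.03 |
| 7.88 | 0.02 | 1.138 | 6.6% | 1.07 |
| 7.88 | 0.03 | 1.206 | 7.4% | 1.10 |
| 7.88 | 0.05 | 1.344 | 9.1% | 1.16 |
| 15 (not the planned recruitment) | 0.05 | 1.700 | 13.3% | 1.30 |

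At ICC 0.05, taking m as 7 or 8 gives 8.6% or 9.2%. With DE 1.344, a nominal 95% interval covers about 91%.

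**4. Simulation check.** 25 professionals per arm, 8 patients each, no true effect, 10,000 runs per setting:

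| ICC | t test | Chi-square | Cluster-level t test (continuous; binary) |
|---|---|---|---|
| 0.01 | 6.0% | 5.6% | 5.1%; 4.7% |
| 0.02 | 6.7% | 6.7% | 5.0%; 4.7% |
| 0.05 | 9.4% | 9.3% | 5.1%; 4.8% |

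The inflation agrees with the formula, and analysing one mean per professional brings the error back to about 5%.

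**5. Power after correction.** With 187 evaluable patients per arm and ICC 0.05, the effective number is 187/1.344 = 139 per arm, which gives about 89% power. With 15 per cluster it is 187/1.70 = 110, which gives about 80%.

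**The case against.** - **A statistical analysis plan may deal with this.** It may, and silence would be no finding. But section 2.3 is not silent: it names methods that do not fit the trial's own randomisation unit.
- **The methods are not all wrong.** This stands. For outcomes measured once per professional, the professional is both the randomised and the analysed unit, and a t test can be appropriate. A reader might infer that section 2.3 assigns these tests to the patient outcomes. It makes no assignment either way; the fault is that one set of methods covers both levels.
- **The excess may be small.** This also stands. It needs a positive ICC, and at 0.01 it is under one percentage point. The article's 0.05 is near the top of its range, so 9% is close to an upper figure.
- **13% error and intervals 30% wider.** A reader might infer these from the 1.7 in section 2.4. That factor assumes 15 patients per professional, which with 394 patients would mean about 26 professionals (394/15), not 50. At 7.88 per professional, 1.7 would need an ICC of 0.7/6.88 = 0.10, twice the article's value. These figures do not describe the planned trial.
- **The strata appear in no model.** A reader might infer this too, but section 2.5.2 records occupation and place of work, and section 2.3 says that work factors enter the multivariable analysis. They are candidate covariates; what is lacking is a commitment to include them. Leaving strata out could also make a test somewhat conservative and offset part of the inflation, but the article gives no figure for this.

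**Conclusion.** The concern holds, limited to patient-level outcomes. The article randomises professionals, budgets for correlation among their patients, and then names only methods that assume independence. The standard error is understated for any positive ICC. At the planned 7–8 patients per professional the true error is about 6% to 9% over ICC 0.01 to 0.05, and correct 95% intervals are up to about 16% wider. This rests on equal cluster sizes and on ICCs no higher than the article states; uneven recruitment across professionals would make the inflation worse. The excess is moderate, but it affects the patient-level primary outcomes and costs little to remove, so section 2.3 should be amended before any analysis.

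**What to change.** In section 2.3:

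1. Separate patient-level from professional-level outcomes.
2. For all patient-level outcomes, require an analysis that accounts for clustering by professional. Examples are a mixed model, or GEE with the professional as cluster, or a cluster-level analysis.
3. If a model is used, add a small-sample correction: Kenward-Roger where it applies, or degrees of freedom equal to the number of professionals minus the cluster-level parameters. A fixed 48 (50 professionals minus two arms) would be too many once centre and type of professional are also in the model.
4. Commit to including the stratification factors: type of professional, and centre as far as the number of centres allows. The article does not give that number.
5. Keep simple t tests only for outcomes measured once per professional.

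The cost is a change of wording and a different procedure. No extra patients are needed while the ICC is at most 0.05, because recruitment already carries a design effect larger than 7–8 patients per professional requires. The downside is wider intervals.

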### 2.2. Materials and methods

Participants’ information will be obtained from validated tools for assessing risky alcohol use (AUDIT) (21) and the motivational interview (EVEM questionnaire) (22). In addition, the Jefferson (23) scale will be used to assess the empathy of healthcare providers in the management of alcohol use.

-AUDIT (21). Tool designed to identify risky alcohol use that comprises 10 questions divided into 3 conceptual domains. The first domain evaluates recent alcohol consumption and contains three questions (frequency of alcohol use, usual amount of alcohol consumption, and frequency of binge drinking). The second domain assesses symptoms of dependence through three items (loss of control over consumption, increased relevance of consumption and morning drinking). The third domain assesses harmful alcohol use through four questions (feeling of guilt after drinking, memory gaps, alcoholrelated injuries and concerns about drinking). A result equal to or above eight is considered indicative of hazardous and harmful consumption, and a possible alcohol dependence.

-Scale for the assessment of the MI (EVEM) (22). A scale of 14 items with a score of 0 to 4, created to assess encounters between professionals and patients using MI. This scale analyzes: (1) empathy; (2) facilitating patient positioning; (3) working in concordance with the patient; (4) using open questions; (5) performing reflective listening; (6) performing summaries; (7) validating the patient; (8) agreeing on change objectives; (9) promoting action/plan design with the patient; (10) Prevents discord with patient; Global Interview Spirit: (11) evokes; (12) collaborates; (13) honors patient autonomy; (14) shows compassion. This scale has been validated by members of this group (24).

-Empathy Scale (Jefferson Scale) (23), which evaluates three dimensions of empathy: Taking perspective, caring with compassion, and standing in the patient’s shoes. It consists of 20 Likert-type questions with a 7-point response range from strongly disagree (score = 1) to strongly agree (score = 7).

-Knowledge and Attitude Questionnaire: Based on the questionnaire created by our team for a previous study (25), and which was subjected to a process of apparent or consensus logical validity and content validity.

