**-Variables measured in patients with risky alcohol use:**

To assess the effectiveness of interventions, the main outcome variables will be the number of SDU in a typical day, the frequency of more than 6 SDU/day, and the total score of the AUDIT (21) questionnaire. All these variables will be considered as primary outcomes.

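### Section 2.3 makes the t test or ANOVA conditional on a Kolmogorov-Smirnov normality check, which is uninformative at 197 patients per arm and leaves the bivariate test for primary outcomes to the data

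*Protocol article*

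**What the plan says.** The Statistical analysis section (2.3) lists a bivariate step to assess the effect of the intervention. It names the chi-square test and a comparison of means for independent samples, "such as Student *t* test or ANOVA (after verification of normality by using the Kolmogorov-Smirnov test"). The significance rule is two-sided: "bilateral comparisons were used, and a value of *p* ≤ 0.05 will be considered". Multiple linear regression and binary logistic regression follow, with no normality condition.

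Section 2.5.1 makes three patient outcomes primary: "the number of SDU in a typical day, the frequency of more than 6 SDU/day, and the total score of the AUDIT" questionnaire. Section 2.2 says that the AUDIT "comprises 10 questions divided into 3 conceptual domains", so its total is a whole-number sum. Section 2.4 sets the size: "the size would be 394 subjects to recruit (197 in each group"). Losses are filled by "dragging for analysis the data from the last observation obtained" (section 2.3), so the number analysed stays close to 197 per arm.

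The article gives no mean, SD or shape for any primary outcome. It does not say whether the Kolmogorov-Smirnov (K-S) test is run with or without the Lilliefors correction for an estimated mean and SD.

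**The concern.** A normality pre-test answers a question that the analysis does not ask. With nearly 200 patients per arm, a t test is valid, as far as normality goes, if the arm means are approximately normal. That holds for a wide range of discrete and skewed data. The K-S test looks at the raw values, and at this size it detects the discreteness and skew that drink counts and questionnaire scores usually have.

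The choice of bivariate test for a primary outcome then depends on features of the data that have little to do with the validity of the t test. The same outcome may pass or fail according to modest skew or a software option that is not stated. A choice made that way is made on unblinded, open-label data. The plan is also uneven: non-normal data may not enter a t test, yet may enter a linear regression that compares adjusted means of the same outcome.

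**Working it through.** **1. The plan's own sample size.** Inputs from section 2.4: "between EG (37%) and CG (20"%), "for an alpha error of 5%, and statistical power of 80"%, ICC 0.05, cluster size 15, loss 5%. With the pooled formula, two-sided and without continuity correction:

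n = [1.96·√(2·0.285·0.715) + 0.8416·√(0.37·0.63 + 0.20·0.80)]² / 0.17² = (1.251 + 0.528)² / 0.0289 ≈ 109.5, so 110 per group.

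Design effect = 1 + (15 − 1)·0.05 = 1.70; 110·1.70 = 187; 187/0.95 = 196.8, so 197 per group. The stated 110 and 197 reproduce, and 197 is the size used below.

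**2. How often the check rejects at n = 197.** K-S against a normal with estimated mean and SD, at 0.05, one arm, 600 simulated samples per shape. The t-test column is the two-sided false-positive rate at 0.05 with identical arms and independent patients (3,000 runs). All shapes are assumptions.

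| Assumed shape | K-S, uncorrected | K-S, Lilliefors | t test false positives |
|---|---|---|---|
| Drinks/day: Poisson mean 4; negative binomial mean 4, SD 3; mean 5, SD 4 | 99.8% each | 100% | 4.8–5.2% |
| Drinks/day: rounded normal, mean 5, SD 2 | 98.8% | 100% | 4.4% |
| Drinks/day: rounded normal, mean 5, SD 3 | 41% | 100% | 5.1% |
| AUDIT: near-symmetric, mean 10–12, SD 4–6 | 0.5–6% | 48–91% | 4.8–5.2% |
| AUDIT: right-skewed, mean 9–12, SD 5–6 | 45–93% | 98–100% | 5.2–5.3% |
| AUDIT: piled up from the cut-off of 8 | 100% | 100% | 5.0% |
| Frequency as a 0–4 item | 100% | 100% | 4.1–4.6% |
| Continuous normal (reference) | 0% | 5% | 4.5% |

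The check moves between almost never and always rejecting, while the t test stays at 4.1–5.3% for every discrete or skewed shape.

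**3. Abstainers.** Section 2.4 expects 20% and 37% of patients in partial or total abstinence. If all of these were total abstainers, they would form a spike at zero. Adding zeros to the drinks/day shape with mean 5, SD 3 raises uncorrected rejection from about 40% to at least 99% with 20% zeros, and to 100% with 37%. For a near-symmetric AUDIT (mean 11, SD 5), with abstainers scoring 0–3, it is 71% and 100%. Since abstinence may be partial, true zeros may be fewer: with 5–10% abstainers the AUDIT figure is only 2–5%.

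**4. What the t-test column leaves out.** It assumes independent patients, but professionals are randomised (section 2.1.3). An unadjusted t test has false-positive rate 2·[1 − Φ(1.96/√DE)].
- At 394/50 = 7.88 patients per professional: DE = 1 + 6.88·0.05 = 1.344, giving 2·[1 − Φ(1.691)] ≈ 9%.
- At the article's DE of 1.7: 2·[1 − Φ(1.503)] ≈ 13%.

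Dropping the normality check is therefore safe for normality only. Its replacement must handle clustering.

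**The case against.** Every rejection rate rests on an assumed distribution, because the article supplies none. That stands, and it limits the claim. A reader might infer that the check would rule out the t test for all the primary outcomes. The figures do not support that: an uncorrected K-S test passes a near-symmetric AUDIT total almost every time, and rejects a wide, near-symmetric drinks/day count in only 41% of samples.

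A reader might also infer that a failed check leaves no planned analysis of these outcomes. It does not. Section 2.3 also names chi-square, linear regression and logistic regression, none of them conditional on normality, and it gives the t test and ANOVA as examples. The frequency of more than 6 SDU/day may be meant for chi-square, so its 100% rejection matters only if someone intended to compare its means.

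Nor do the documents support a matching claim about the roughly 25 professionals per arm. Their outcomes include long sum scores such as EVEM (14 items scored 0–4) and the Jefferson scale (20 items scored 1–7). The shapes examined here are patient drinking data.

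That no alternative test is named is no fault in a condensed article, and no particular fallback should be presumed. What remains is a rule that the article itself states, and it is badly chosen for these outcomes at this size.

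**Conclusion.** The point holds in a limited form. The normality condition on the bivariate t test or ANOVA is uninformative at about 197 patients per arm. Under the assumed shapes it nearly always excludes the t test for a skewed drinks/day count. For the AUDIT total it gives anything from under 5% to 100% rejection, according to skew and an unstated version of the test. In neither case does rejection indicate that the t test would fail on grounds of normality.

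The consequence is a data-dependent choice of bivariate test for primary outcomes, and a mismatch with the unconditional linear regression. This does not invalidate the trial or remove every planned comparison of means. It should be corrected before the data are analysed. The conclusion rests on the assumed distributions and, for the t test's 4.1–5.3%, on independence between patients. It does not endorse an unadjusted t test.

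**What to change.** In section 2.3, delete the parenthesis that makes the t test or ANOVA follow a Kolmogorov-Smirnov check. Fix one comparison for each patient primary outcome, to be used whatever a normality test shows:

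- **SDU on a typical day and AUDIT total:** the between-arm mean difference with 95% CI from a model that accounts for clustering by professional (a mixed model, or cluster-robust or cluster-bootstrap standard errors). Ordinary robust or bootstrap standard errors that treat patients as independent would not do.
- **Frequency of more than 6 SDU/day:** a cluster-adjusted ordinal or categorical analysis.
- **Rank tests:** sensitivity analyses only.

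The change is a short edit to the analysis section. It needs no new data and no change to the sample size, and it adds slightly to the analysis work.

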**-Variables measured in patients with risky alcohol use:**

The following variables will be measured in patients with risky alcohol use: age, sex, previous interventions, marital status, education level, place of residence, weight, height, body mass index (BMI), associated diseases, hygiene-dietary habits (such as smoking–number of cigarettes per day- and coffee consumption–number of coffees per day), and stage of change according to Prochaska and DiClemente’s Transtheoretical Model (18). We will also ask participants their opinion about their own alcohol consumption and its consequences in health through an open-ended question. Table 1 shows the variables that will be measured in participants at each follow-up visit.

**TABLE 1 T1:** Variables to be measured at each follow-up visit.

Variables	Follow-up visits				
	**Baseline visit**	**1-month visit**	**3-month visit**	**6-month visit**	**12-month visit**
Socio-demographic characteristics	x				
Clinical measures: weight, height, body mass index (BMI), associated diseases, hygienic-dietary habits (smoking and coffee consumption).	x				
Alcohol consumption opinion	x	x	x	x	x
Standard drink units (SDU)/day of alcohol consumption	x	x	x	x	x
AUDIT questionnaire	x		X	x	x
Scale for the assessment of the motivational interview (EVEM)	x		x	x	
Stage of change regarding alcohol consumption	x	x	x	x	x

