#### 3.1.2. Limitations

It is necessary to keep in mind and recognize the possible bias known as the Hawthorne effect (observer bias) (31), which is inevitable or difficult to minimize in this type of experimental study, in which subjects usually change their behavior by the fact that they feel observed. If there is a high rate of professional or patient dropouts, withdrawals, or losses, the selection bias may become so important that can alter the actual results. Biases of information may occur due to the possible lack of sincerity of the respondent in answering questions regarding knowledge and attitudes regarding their alcohol consumption. Confusion biases will be controlled by multivariate analysis.

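### Section 2.3 names only unadjusted tests for the intervention effect and misdescribes its one regression; baseline drinking and the stratification factors are not named as covariates

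*Protocol article*

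**What the plan says.** - **Tests of effect.** Section 2.3 of the protocol article plans a descriptive and comparability analysis, then bivariate tests of the intervention effect: Chi-square, Student t for independent samples, or ANOVA. They are two-sided ("bilateral comparisons were used").
- **The one regression.** The next step reads: "A multivariate analysis will then be performed to determine which sociodemographic, work, and care factors are associated with the intervention developed". The sentence goes on to mention control of unnamed predictors or confounders, using multiple linear and binary logistic regression. Section 3.1.2 relies on this step: "Confusion biases will be controlled by multivariate analysis".
- **Outcomes.** Section 2.5.1 gives three patient primary outcomes: SDU on a typical day, frequency of more than 6 SDU per day, and total AUDIT score.
- **Baseline data.** Table 1 in Section 2.5.2 schedules "Standard drink units (SDU)/day of alcohol consumption" at baseline and every later visit, and AUDIT at baseline, 3, 6 and 12 months. The written list of patient independent variables in that section includes cigarettes and coffee per day but neither SDU nor AUDIT.
- **Allocation.** Section 2.1.3 randomises professionals 1:1, "stratifying according to the center and type of professional". Section 2.3 does not name these factors as model terms.

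**The concern.** The trial's question is whether drinking differs between arms. The tests named for that question, as described, take no covariates. The one analysis that could take them is given a different target. Arm was assigned at random, so finding which factors go with it says nothing about the effect of motivational interviewing on drinking. Nor can a model with that target do the confounding control that Section 3.1.2 asks of it.

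Baseline drinking matters in this design for two reasons. Patients qualify through weekly intake, AUDIT of 8 or more, or binge drinking (Section 2.1.1.2), so starting levels will vary widely. The randomised units are about 50 professionals, 25 per arm, who know their allocation and recruit their own patients opportunistically. Imbalance in baseline drinking is therefore plausible, by chance or through recruitment. What is at stake is precision and protection against such imbalance.

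**Working it through.** **1. The plan's own figure.** Section 2.4 uses 37% against 20% abstinence, "for an alpha error of 5%, and statistical power of 80" per cent. With a two-sided test, pooled variance and no continuity correction, the mean proportion is 0.285 and

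n = [1.960·√(2·0.285·0.715) + 0.842·√(0.37·0.63 + 0.20·0.80)]² / 0.17² = 109.5, so 110 per group.

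The design effect is 1 + (15 − 1)·0.05 = 1.70. Then 110·1.70 = 187, and 187/0.95 = 196.8, so 197 per group and 394 in total. The stated size reproduces. It rests on an unadjusted comparison of two proportions and takes no credit for baseline values.

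**2. Where baseline drinking appears in the plan.**

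| Place | Role of SDU and AUDIT |
|---|---|
| 2.5.1 | Outcomes |
| Table 1 | Measured at baseline and follow-up |
| 2.5.2, written list | Absent |
| 2.3, tests of effect | No covariates |
| 2.3, regression | Factor classes are sociodemographic, work and care; confounders unnamed |

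The named step most likely to use the baseline values is the initial comparability analysis, which does not estimate an effect.

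**3. What adjustment could gain on a continuous outcome (SDU, AUDIT).** The documents give neither a standard deviation nor a baseline-to-12-month correlation r, so r is assumed over 0.3 to 0.7 and taken as equal at patient and cluster level. Relative to an unadjusted comparison of follow-up values, the variance is multiplied by 1 − r². Effective size per group is 197·0.95/1.7 = 110. In SD units, the difference detectable with 80% power is (1.960 + 0.842)·√(2/110)·√(1 − r²). Power is shown for an assumed true difference of 0.30 SD.

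| r | 1 − r² | Variance removed | Detectable difference | Power at 0.30 SD |
|---|---|---|---|---|
| unadjusted | 1 | 0 | 0.38 SD | 60% |
| 0.3 | 0.91 | 9% | 0.36 SD | 65% |
| 0.5 | 0.75 | 25% | 0.33 SD | 73% |
| 0.7 | 0.51 | 49% | 0.27 SD | 88% |

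**4. If the tests were applied to change from baseline.** With equal variances at both times, a change score has variance 2(1 − r) in units of the follow-up variance: 1.4, 1.0 and 0.6 for r = 0.3, 0.5 and 0.7. The adjusted analysis relative to that is (1 − r²)/[2(1 − r)] = (1 + r)/2, or 0.65, 0.75 and 0.85. Adjustment still gains, by 35%, 25% and 15%, but the range in step 3 is then not the right comparison.

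**5. Binary abstinence.** The factor 1 − r² belongs to linear models. Adjusting a logistic regression does not reduce variance by r², so none of these figures applies to the endpoint in Section 2.4.

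**The case against.** The strongest reply is that the regression sentence is only loosely phrased. A two-level allocation cannot sensibly be the dependent variable of a multiple linear regression. The linear and logistic pair fits the outcomes: linear for SDU and AUDIT, logistic for abstinence. The same sentence speaks of controlling confounders. This stands. A reader might infer that the arm effect will never be estimated with adjustment, and the text does not support going that far. Even on the kinder reading, though, the stated aim is wrong and no baseline outcome is named.

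A second reply is that baseline may enter through the outcome. Section 3.1.1 counts patients who reduce consumption or reach abstinence as successes, and reduction is measured against baseline. This is fair, so it cannot be said that baseline is ignored altogether. But Section 2.3 does not say that change is what is tested, and step 4 shows that adjustment would still help.

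A third is that covariate lists belong in the full protocol or analysis plan. A missing list alone would be no finding. Here the article itself states the unadjusted tests and the regression's aim, and a plan that followed those words would carry the problem forward.

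A reader might also infer that covariates will be picked after looking at baseline differences, because the comparability analysis comes first. The article does not say so: the order of steps is not a selection rule. Nor is an unadjusted randomised comparison biased merely because it omits baseline.

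**Conclusion.** The point holds as a flaw in the stated analysis and an improvement available at almost no cost. Section 2.3 commits to unadjusted tests, misstates the target of its only regression, and names neither the baseline outcome nor the stratification factors as covariates. The sample size arithmetic is unaffected.

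The gain for SDU and AUDIT is a 9% to 49% fall in residual variance. It is conditional on an assumed correlation of 0.3 to 0.7, equal at patient and cluster level, and on a follow-up-only comparison as the alternative. It is tempting to turn this into a saving in patients for the trial as a whole, since 1/(1 − r²) − 1 gives 10% to 96%. The documents do not support that: they supply no correlation, and the trial was sized on a binary endpoint to which the formula does not apply.

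**What to change.** Reword Section 2.3 as follows:

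- Make each patient primary outcome at 12 months the dependent variable and arm the exposure. Prespecify the baseline value of that outcome, centre and type of professional as covariates.
- Account for clustering by professional, with a random effect or GEE. The article does not give the number of centres, so settle in advance how centre enters a model with about 50 professionals.
- For a binary abstinence outcome, adjust for baseline SDU and AUDIT.
- Label any search for predictors of change exploratory, with the drinking outcome as the dependent variable.
- Align the confounding statement in Section 3.1.2 with this model, and name baseline SDU and AUDIT among the covariates in Section 2.5.2.

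The cost is wording. Baseline SDU and AUDIT are already scheduled, and centre and type of professional are known at randomisation. One detail needs confirming: the frequency of more than 6 SDU per day has no row of its own in Table 1. Its baseline value is available without new data if it is taken from the AUDIT question on binge-drinking frequency, which the article does not state.
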